# Improving caring quality for people with dementia in nursing homes using IPOS‐Dem: A stepped‐wedge cluster randomized controlled trial protocol

**DOI:** 10.1111/jan.14953

**Published:** 2021-07-07

**Keywords:** caring, dementia, family, needs, nursing, nursing home, palliative care, quality of life

## Abstract

**Aims:**

We aim to evaluate the effectiveness of the Integrated Palliative Care Outcome Scale for people with dementia‐based case studies to improve the caring quality for people with dementia in nursing homes by frontline staff and family members.

**Background:**

Swiss nursing homes mostly care for people with dementia. This population is at high risk of receiving little to no palliation for their complex needs. The majority of Swiss frontline healthcare staff do not systematically report on the needs of their residents. Additionally, family members do not routinely participate in assessment processes.

**Design:**

We will conduct a stepped‐wedge cluster randomized trial of repeated assessment using the Integrated Palliative Care Outcome Scale for people with dementia (IPOS‐Dem) and subsequent case studies. Clusters will consist of Swiss nursing homes randomly assigned to one of three sequential intervention time points.

**Methods:**

The study population will consist of people with dementia living in nursing homes with and without specialized dementia care facilities. Over 16 months, staff working at the frontline and family members will assess the needs and concerns of people with dementia using IPOS‐Dem. Depending on sequence allocation, facilitated case studies will start after 3, 6 or 9 months. The primary outcome will be caring quality measured by QUALIDEM. The secondary outcome will be symptoms and concerns, as indicated by the IPOS‐Dem sum‐score. The Zürich Ethics Committee approved the study in 2019 (2019‐01847).

**Impact:**

The results of this study will contribute to improving the effectiveness of person‐centred care for people with dementia. Collaboration between healthcare staff and family members will be systematically developed and built upon thorough assessment using the IPOS‐Dem and related case studies. The use of IPOS‐Dem will offer all frontline staff a systematic approach to have an independent voice within the nursing process, regardless of their qualification or grade.

## INTRODUCTION

1

Dementia is an umbrella term for several neurological conditions that progress to impaired functioning and cognition and the inability to perform daily life activities (Livingston et al., 2020). According to Sleeman et al., (2019), people with moderate to severe stages of dementia (PWD) face the prospect of health‐related suffering. There is evidence that PWD have inadequate access to palliative care for their complex needs (Knaul et al., 2018; Sleeman et al., 2019). The complexity of caring for PWD arises from their multi‐dimensional needs, which in turn influence the individuals’ health and limit accurate prognostic assertions, palliation and treatment (Grünig, 2014, p. 9; Livingston et al., 2020). The quality of life and caring of PWD and their families are compounded by untreated and undertreated symptoms, unmet needs, and undisclosed wishes and choices (Deuschl & Maier, 2016; Husebø et al., 2011; Shim et al., 2016).

In 2009, Ecoplan (2013) estimated that about 130,000 PWD were living in Switzerland. More than 65% of PWD were aged 80 years or older. The number of PWD in Switzerland is projected to increase to 280,000 by 2050 (Ecoplan, 2013). Similarly, Livingston (2020) reported 50 million PWD worldwide, with a three‐fold increase projected by 2050. As their disease progresses, most PWD eventually move into nursing homes (Livingston et al., 2020). In Switzerland, as in most European countries, 65% of nursing home residents have dementia (Ecoplan, 2019; Onder et al., 2012).

Registered nurses (RN) in Swiss nursing homes usually provide nursing care collaborating with nursing associate professionals, healthcare assistants and other personnel (Zúñiga et al., 2021). In the German‐speaking part of Switzerland, RN make up 30% of the grade mix in nursing homes, 41% of their colleagues are nursing associate professionals, and 30% are trainees, interns and assistant staff (Zúñiga et al., 2021). Nursing homes in Switzerland have a broad organizational staff skill mix. An RN in Switzerland usually monitors the nursing process and medical management and delegates some direct care activities. Sometimes, RN in Swiss nursing homes are involved with quality and innovation (Zúñiga et al., 2021). Frontline staff in nursing homes establish caring relationships based on systematic observation of needs (Koppitz et al., 2013). For this study, and like that articulated by Watson (2008), caring is defined as a moral imperative and ethical foundation of nursing. When engaging in caring, frontline staff in nursing homes are not merely performing instrumental tasks but performing conscious and intentional forms of ‘being’ (Turkel et al., 2018; Watson, 2008).

## BACKGROUND

2

Frontline staff in nursing homes have a challenging role; when caring for PWD, they frequently evaluate needs, medical symptoms and possibly undisclosed choices and wishes. They must monitor PWD for their needs and concerns, despite PWD having impaired cognitive abilities that influence their ability to report medical symptoms and corresponding needs (Lichtner et al., 2014). Caring in nursing homes is a collaborative task. Still, miscommunication between a staff member and a PWD or other frontline staff or family members may impede the complete detection and subsequent management of issues (Ellis‐Smith et al., 2018; Krumm et al., 2014). In Swiss nursing homes, processes for routine assessments are in place, e.g., Resident Assessment Instrument, ‘Bewohner/‐in‐ nen‐Einstufungs‐ und –Abrechnungssystem’ and ‘Planification Informatisée des Soins Infirmiers Requis’ (RAI, BESA and PLAISIR). However, the processes and policies attached to these routine assessments appear to prevent timely and relevant monitoring of PWD (Boyd et al., 2014; Koppitz et al., 2016). Two‐thirds of the frontline staff in nursing homes are not formally permitted to document their observations in routine assessments, leading to a deficit in their capacity to elicit critical concerns for PWD (Obsan, 2009; Vettori et al., 2017).

The instruments and processes in use also neglect family members’ perspectives and their consequential disclosure of current and prior decisions of PWD (Vettori et al., 2017). Processes and proposed interventions to foster family involvement in nursing homes are heterogeneous (Backhaus et al., 2020), although the unique perspectives of family members to augment the framing of quality of life, developments and caring quality of PWD are well‐documented (Ellis‐Smith et al., 2018; Robertson et al., 2019). A structured, systematic symptom and needs assessment that fosters communication between family caregivers and frontline staff may help recognize unmet needs and enable family caregivers to gain insight into PWD (Backhaus et al., 2020; Ellis‐Smith et al., 2016, 2018). The use of the Integrated Palliative care Outcome Scale for Dementia (IPOS‐Dem) helps carers to recognize symptoms and concerns of PWD (Cicely Saunders Institute (CSI), 2018a). The brief and easy‐to‐use IPOS‐Dem is built on a comprehensive family of proxy and patient‐reported outcome measures for palliative care (Cicely Saunders Institute (CSI), 2015). The IPOS‐Dem informs an overview of the quality of life and caring quality for PWD with its holistic and multi‐dimensional perspective (Ellis‐Smith et al., 2018). Quality of life for PWD is considered by disease severity and individual and environmental factors (Ettema et al., 2007b). Furthermore, Banerjee et al., (2009) conceptualized quality of life for PWD as multi‐dimensional well‐being in various domains. Therefore, the quality of life for PWD seems to be sensitive to psychological and behavioural symptoms, cognitive and functional decline and the caring quality a PWD experiences (Banerjee et al., 2009; Koppitz et al., 2013).

Ellis‐Smith (2018) reported that the use of the IPOS‐Dem improved aspects of caring quality for PWD. Quality of care, caring quality and quality of life seem closely interrelated, especially for PWD (Koppitz et al., 2013). Caring quality for PWD can be captured in the QUALIDEM.

Establishing a shared value set and management strategies based on the needs, concerns and collaborative observations of PWD is crucial to improving caring quality for PWD. Implementation of regular, systematic assessment of PWD in nursing homes is a prerequisite (Haan et al., 2018; Kupeli et al., 2016).

## THE STUDY

3

### Aims

3.1

We aim to evaluate the effectiveness of case studies based on a structured needs assessment using the IPOS‐Dem to improve caring quality and quality of life for PWD in Swiss‐German nursing homes by frontline staff and family members.

### Design

3.2

We propose a stepped‐wedge cluster randomized trial (SW‐CRT) design (Hemming et al., 2015; Hemming et al., 2015) to examine the objectives. An SW‐CRT starts without exposing the clusters, nursing homes in our case, to the intervention to allow for baseline data collection. During study conduct, the clusters or cluster groups are exposed to the intervention in a step‐wise fashion, occurring after regular intervals until all clusters are exposed to the intervention. We will employ mixed‐effects models, i.e., random effects, to adjust for cluster‐specific factors and repeated measures design. This trial will evaluate whether structured symptom assessment and subsequent case studies augment caring quality for PWD. The intervention will be assessed by (1) caring quality with the QUALIDEM and (2) changes in identified needs, as assessed by the IPOS‐Dem.

The SW‐CRT has three advantages for our study. Firstly, the design allows long‐term effects, i.e., trends, to be assessed during the study (Jordan et al., 2015). One expected trend is that the caring quality, as measured by the QUALIDEM, will improve over time. The implementation of purposive data collection using the IPOS‐Dem, representing the control condition, could also be interpreted as a trend by itself, with a learning curve for frontline staff. The stepped‐wedge design will enable an objective assessment of both trends during the trial. Secondly, we aim to offer nursing home management boards added value for their residents through using an SW‐CRT because exposure to the case study intervention for 6 months is guaranteed. Thirdly, our case study intervention is dependent on the observations of frontline staff and family members using IPOS‐Dem, which promotes inclusivity and participation. Introducing the intervention en bloc was considered challenging regarding logistics regarding the aforementioned prerequisite and the complexity of the case study intervention. Therefore, we will employ measurements at fixed periods across the trial duration in participating nursing homes and consider the time effects in the models for analysis (Haines & Hemming, 2018). In other words, the presumed effect of the implementation of the IPOS‐Dem and QUALIDEM will be levelled out by the time the intervention commences.

Data collection will occur over 15 months, with frontline staff and family caregivers collecting data each month from the same participants (i.e., a closed cohort). We will randomly allocate participating nursing homes to three groups. The three groups will cross over at different time points from the control condition to the intervention condition; they will cross over with steps 3, 6 and 9 months after the trial starts. In an SW‐CRT design, the nursing homes can enrol in the study at different absolute time points as long as the planned sequence of measurement, conditions and steps are followed through as planned. An SW‐CRT, therefore, greatly improves the feasibility for the study team.

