### Outcomes

3.7

We will assess the study outcomes in the sequence relative to the nursing home, as illustrated in Table 2. The scales and measures to be implemented are the German versions of the QUALIDEM (Dichter et al., 2011; Ettema et al., 2007a, 2007b) and the Swiss‐German adaptation of the IPOS‐Dem. Both the QUALIDEM and IPOS‐Dem will be assessed on a cluster and an individual nursing home level.

**TABLE 2 jan14953-tbl-0002:** Sequence of outcome assessment

Outcomes	Measured at the beginning of period
Socio‐demographics	T0
BESA/RAI MDS	T0
QUALIDEM	T0, T3, T6, T9, T12 and T14
IPOS‐Dem	T0, T1, T2, T3, T4, T5, T6, T7, T8, T9, T10, T11, T12, T13 and T14

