### Sample size calculation

3.9

The sample size was calculated using simulations for a cohort stepped‐wedge design. The primary outcome would be repeatedly obtained from the same participants within each cluster (nursing home), as in previous similar studies (Aegerter et al., 2020). Based on previous QUALIDEM results, we assumed a baseline mean of 71.3 and a standard deviation of 16.7 (van Dam et al., 2019). The number of nursing homes was set to 20 with three cluster groups. The attributable difference in the QUALIDEM was expected to be around 5%, as derived from clinical expertise. We set the number of steps to three for practical reasons (study rollout). After baseline measurement, nursing homes will switch from the control condition to the intervention condition at given periods until all nursing homes are applying the intervention regime. To determine the appropriate sample size, we varied the average cluster size in our simulation over a range of 4 to 16 subjects per cluster. We assessed the sensitivity of the sample size calculations by varying the cluster‐specific and subject‐specific ICC. More specifically, we used ICC values for Rho[1] = {0.1, 0.2} and Rho[2] = {0.2, 0.3}, respectively. In our simulation, we used a standard closed cohort mixed‐effects model. The latter comprised a random effect for the clusters (*α*) and a random effect for the repeated measurements on the same cohort of individuals (*ζ*). Moreover, the model included a fixed effect to account for time trends (*β*) and a fixed effect representing the treatment effect (*θ*).
(1)
$$y=\mu_{\mathrm{ij}}+e_{\mathrm{ijk}}$$

(2)
$$\mu_{\mathrm{ij}}=\mu +\alpha_{i}+\zeta_{\mathrm{ik}}+\beta_{j}+X_{\mathrm{ij}}\theta$$

(3)
$$\zeta_{\mathrm{ik}}∼N\left(0,\sigma_{\zeta }^{2}\right)$$

(4)
$$\alpha_{i}∼N\left(0,\sigma_{\alpha }^{2}\right)$$

(5)
$$e_{\mathrm{ijk}}∼N\left(0,\sigma_{e}^{2}\right)$$

To estimate our models, we used the linear mixed‐effect method (lmer) from the R‐package lme4 (Bolker et al., 2021). Furthermore, we set the acceptance probability for a Type I Error to *p* = .05 and the acceptance probability for a Type II Error to *p* = .20 (power = 0.80).

The required sample sizes to achieve the desired power of 0.80, given the aforementioned parameters and assumptions, are shown in the two scenarios plotted in Figure 1.

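### Homes may start at different calendar dates, but the one written model has no calendar term, so seasons or regional outbreaks can make the standard error of the treatment effect too small

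*Protocol article*

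**What the plan says.** The protocol article's Design section (3.2) says that homes "can enrol in the study at different absolute time points as long as the planned sequence of measurement, conditions and steps are followed", and offers this as a gain in feasibility. Crossover is fixed by elapsed time: "they will cross over with steps 3, 6 and 9 months after the trial starts". The Outcomes section (3.7) states "We will assess the study outcomes in the sequence relative to the nursing home", and Table 2 places QUALIDEM at "T0, T3, T6, T9, T12 and T14".

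The one model given as an equation is in the sample size section (3.9). "The latter comprised a random effect for the clusters", with a further random effect for residents, and "the model included a fixed effect to account for time trends". Equation (2) therefore holds a home intercept, a resident intercept, one period effect β_j and the treatment effect θ. For the analysis, the Design section promises only to "consider the time effects in the models for analysis". The Statistical analyses section (3.11) lists resident characteristics measured at baseline as adjustment factors. Study settings (3.3) describes random allocation of homes to three sequences and mentions no link to start date.

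**The concern.** Within every home, control comes before intervention. A stepped wedge separates treatment from time by comparing homes that are in different conditions in the same period. If all homes start together, period j is one stretch of calendar time and β_j removes whatever happened in it. If starts are staggered and j counts from each home's own start, homes share elapsed time but not the calendar. A winter may then fall at T3 in one home and T9 in another.

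β_j cannot absorb that, and baseline covariates, which are constant over follow-up, cannot either. The disturbance is common to all residents of a home at that visit, but the model treats it as independent residual error between residents. The confidence interval for θ would then be too narrow and a false positive more likely than the nominal 5%.

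**Working it through.** **Inputs from the protocol (section 3.9).** SD 16.7; ICC pair 0.1 and 0.2; a difference of 5%, taken as 5 points; 20 homes of 10 residents for the power claim; 22 homes of 10 with six measurements as the final design; alpha 0.05, taken as two-sided.

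**Assumed, because the protocol gives no figure.** The spread of start dates, and the shape and size of any calendar effect.

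**Step 1: the plan's own figure.** For equations (1)–(5), Var(θ̂) is the θ element of (D′V⁻¹D)⁻¹, with D the fixed-effect design matrix and V the covariance matrix. Power is Φ(5/SE − 1.96). With 20 × 10 this gives 0.787 (four periods, ICCs taken as additive) or 0.790 (six measurements, ICCs taken as nested), against the stated 0.80. The model is therefore read correctly enough for this purpose.

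**Step 2: which calendar effects survive.** Let home i start at s_i and let t_j be time since start, so calendar time is s_i + t_j.
- Linear trend: γ(s_i + t_j) = γs_i + γt_j. The first part goes into the home intercept and the second into β_j, so nothing is left over.
- Non-linear effect f(s_i + t_j): this does not split into a home part plus a period part. The remainder varies by home and period, and equation (2) has no term for it.

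**Step 3: size.** The final design was simulated with true effect 0, sequence independent of start month, and the written model fitted by REML (1,000–2,000 runs per cell, Monte Carlo error about 0.5–1 percentage point). Type I error:

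| Assumed calendar effect | Common start | Starts over 6 months | 12 months | 18 months |
|---|---|---|---|---|
| None | – | – | 4.3% | – |
| Season ±3 points | 5.5% | 8.3% | 9.3% | 8.5% |
| Season ±5 points | 5.2% | 12.5% | 15.6% | 16.0% |
| 4-month outbreak, 5 points | 6.6% | – | 7.2% | 6.9% |
| 4-month outbreak, 10 points | 4.4% | – | 13.4% | 11.9% |
| Linear trend, 3 points a year | – | – | 5.9% | – |
| Linear trend, 5 points a year | – | – | 4.3% | 4.1% |

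Repeat simulations under other settings gave, for a season of ±3, 7.3% (6 months) and 10.5–11.2% (12 months); for ±5 over 12 months, 16.8%; and for an 8-point dip, 9.1–14.1%. Smaller effects do little: a season of ±1 gives 5.1–5.6%, ±1.5 gives 5.5–6.0%, and a 3-point dip gives 5.7%. For the 5-point outbreak, the gap from a common start is within Monte Carlo error.

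**Step 4: where the excess comes from.** The mean estimate stayed within about 0.1 point of zero throughout. The standard error is what fails. If the estimate has true SD S but the test uses standard error M, type I error is 2[1 − Φ(1.96 M/S)].
- Season ±3, 12 months: 1.96 × 1.619/1.873 = 1.694, giving 9.0% (simulated 9.3%).
- Season ±5, 12 months: 1.96 × 1.652/2.292 = 1.413, giving 15.8% (simulated 15.6%).
- Outbreak of 10, 12 months: 1.96 × 1.649/2.157 = 1.498, giving 13.4% (simulated 13.4%).

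**Step 5: two remedies, 12-month spread (1,500 runs each).**

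| Assumed effect | Written model | Plus calendar quarter | Variance at home-period level, t on 20 df |
|---|---|---|---|
| None | 4.4% | 3.8% | 3.2% |
| Season ±3 | 8.7% | 5.3% | 5.3% |
| Season ±5 | 16.8% | 6.6% | 7.5% |
| Outbreak 5 | 6.1% | 5.1% | 3.5% |
| Outbreak 10 | 12.5% | 7.3% | 4.5% |

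**The case against.** Several points on the other side have force.

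- **Equation (2) is the sample-size simulation model.** Section 3.11 gives no equation and its covariate list is illustrative. An analysis plan not shown here could code time differently. That j counts home time is an inference from sections 3.2, 3.7 and 3.9, and the crossover wording could be read as counting from one common trial start. This stands as a limit on certainty. It does not remove the point, because the protocol expressly permits staggered starts and ties outcome timing to the home, while its one written model has nothing that would deal with the consequence.
- **Home-specific shocks are a separate matter.** Independent 8-point, 4-month dips in each home gave type I error of 13.1% with a common start, 12.9% with staggered starts, and 13.0% after adding calendar quarter. That is a missing home-by-period term. Staggering does not cause it and calendar quarter does not cure it.
- **The calendar effects are assumed.** An 8-point dip exceeds the planned 5-point difference, and at ±1.5 points or less the problem almost vanishes. This stands, and is why a range is given.

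A reader might also infer that ordinary secular change goes unadjusted, or that θ is biased. Steps 2 to 4 contradict both while sequence is independent of start date. Chance imbalance of start dates between sequences is the same extra variance, not a second fault. Nor does the protocol say that start date is immaterial; it says that homes may enrol at different times, as a point of feasibility.

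**Conclusion.** The point holds in a limited form. If starts are staggered and the period effect counts time since each home's start, a non-linear calendar effect shared by homes leaves the standard error of θ too small. In the worst case tried, the model reported about 1.65 against an empirical 2.35. The estimate remains unbiased on average and linear trends are harmless.

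Over starts spread across 6 to 18 months, type I error is about:
- 5–6% for a season of ±1.5 points or less;
- 6–11% for ±3;
- 12–17% for ±5;
- 6–7% for a 5-point outbreak dip;
- 9–14% for dips of 8 to 10 points.

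With a common start it is about 5%. These are conditional figures: the protocol gives neither the spread of start dates nor the size of any calendar effect, so they do not show that this trial's error rate will be inflated. They concern the six-measurement QUALIDEM analysis; the monthly IPOS-Dem model was not simulated, though the same reasoning applies to it.

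**What to change.** 1. State that j is time since each home's start, and record the calendar date of every assessment. Section 3.10 mentions date fields only as an example of format checks, so this should be made explicit.
2. Add calendar-quarter fixed effects beside time since start in the QUALIDEM and IPOS-Dem models. This is several terms: starts over 12 months plus 14 months of follow-up span 26 months, or about nine quarters and eight contrasts. The linear parts of the two clocks cannot be separated within a home, so their coefficients should not be interpreted singly.
3. Preferably also add a home-by-period random effect with a small-sample correction, since calendar quarter only partly corrects short dips and does nothing for shocks confined to one home.
4. If homes start in waves, randomise sequence within wave.
5. Qualify the sentence in section 3.2 to say that staggered starts require calendar-time adjustment.

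Cost of the quarter terms when there is no calendar effect: the standard error goes from 1.60 to 1.65 (1.65/1.60 = 1.03). Power for 5 points goes from Φ(5/1.60 − 1.96) = 0.88 to Φ(5/1.65 − 1.96) = 0.86, still above 0.80 with 22 homes of 10 and complete data.
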